## Abstract

**Background:**

Current theories of tinnitus assume that the phantom sound is generated either through increased spontaneous activity of neurons in the auditory brain, or through pathological temporal firing patterns of the spontaneous neuronal discharge, or a combination of both factors. With this in mind, Tass and colleagues recently tested a number of temporally patterned acoustic stimulation strategies in a proof of concept study. Potential therapeutic sound regimes were derived according to a paradigm assumed to disrupt hypersynchronous neuronal activity, and promote plasticity mechanisms that stabilize a state of asynchronous spontaneous activity. This would correspond to a permanent reduction of tinnitus. The proof of concept study, conducted in Germany, confirmed the safety of the acoustic stimuli for use in tinnitus, and exploratory results indicated modulation of tinnitus-related pathological synchronous activity with potential therapeutic benefit. The most effective stimulation paradigm is now in clinical use as a sound therapy device, the acoustic coordinated reset (CR®) neuromodulation (Adaptive Neuromodulation GmbH (ANM), Köln, Germany).

**Methods/Design:**

To measure the efficacy of CR® neuromodulation, we devised a powered, two-center, randomized controlled trial (RCT) compliant with the reporting standards defined in the Consolidated Standards of Reporting Trials (CONSORT) Statement. The RCT design also addresses the recent call for international standards within the tinnitus community for high-quality clinical trials. The design uses a between-subjects comparison with minimized allocation of participants to treatment and placebo groups. A minimization approach was selected to ensure that the two groups are balanced with respect to age, gender, hearing, and baseline tinnitus severity. The protocol ensures double blinding, with crossover of the placebo group to receive the proprietary intervention after 12 weeks. The primary endpoints are the pre- and post-treatment measures that provide the primary measures of efficacy, namely a validated and sensitive questionnaire measure of the functional impact of tinnitus. The trial is also designed to capture secondary changes in tinnitus handicap, quality (pitch, loudness, bandwidth), and changes in tinnitus-related pathological synchronous brain activity using electroencephalography (EEG).

**Discussion:**

This RCT was designed to provide a confident high-level estimate of the efficacy of sound therapy using CR® neuromodulation compared to a well-matched placebo intervention, and uniquely in terms of sound therapy, examine the physiological effects of the intervention against its putative mechanism of action.

**Trial registration:**

ClinicalTrials.gov, NCT01541969

## Background

The phantom auditory sensation of tinnitus is transiently experienced by most people, but for 10 to 15% of the population, and up to one in three of older adults, the experience is chronic [1,2]. Although factors contributing to tinnitus potentially include otologic, neurologic, infectious, and drug-related effects, it is most readily associated with noise exposure and aging [3-5]. Among the most frequently reported difficulties associated with tinnitus are sleep disturbance, hearing difficulties, social withdrawal, and negative emotional reactions, such as anxiety and depression [6-10]. Intrusive tinnitus is, therefore, a complex condition that arises with different etiologies and comorbidities. Management of tinnitus typically involves relieving the distress, anxiety or depression that can accompany tinnitus, masking the sound by introducing external sound, or reducing the neural signal believed to be causing the tinnitus.

Current theories of tinnitus assume that the phantom sound is generated either through increased spontaneous activity of neurons in the auditory brain, or through pathological synchrony of the spontaneous neuronal discharge, or a combination of both factors (see Roberts *et al*. for a review [11]). Theoretical modeling studies indicate that such aberrant activity patterns might be reduced through acoustic stimulation [12,13]. While Schaette and Kempter [12] proposed that sound enrichment provided by prolonged use of a hearing aid could counteract neuronal hyperactivity and reduce tinnitus, Tass and Popovych [13] proposed using sound to interrupt pathological connectivity and synchronous firing that may underlie tinnitus in a process termed ‘coordinated reset’ (CR®). CR® was first modeled computationally by Tass [14] as a method using high-frequency pulse trains to desynchronize the concerted activity of neural subpopulations. Tass *et al*. [15] later generated evidence for applications in the domain of deep brain electrical stimulation for neurological diseases, such as Parkinson’s disease, using an animal model. Given that the model of CR® was not specific to electrical stimuli, Tass and Popovych [13] also modeled the potential CR® effects of acoustic stimulation on tinnitus-related brain activity, concluding it to hold promise as a tinnitus treatment. Tass *et al*. [16] recently conducted a proof of concept study on humans testing acoustic CR® algorithms predicted to disrupt hypersynchronous neuronal activity, and to promote plasticity that stabilizes a state of asynchronous spontaneous activity. Such an effect would correspond to a permanent reduction of tinnitus [13]. The most effective stimulus paradigm is now in clinical use as a sound therapy device, the acoustic CR® neuromodulation (Adaptive Neuromodulation GmbH (ANM), Köln, Germany). While the proof of concept study conducted by Tass *et al*. [16] confirmed the safety of the sound stimulus, it also provided exploratory level evidence that CR® neuromodulation may be efficacious, in terms of reducing the reaction to tinnitus and modulating tinnitus-related pathological synchronous activity. However, a Phase 2 clinical trial is now required to determine efficacy in a controlled and powered sample.

### Purpose

This Phase 2 randomized controlled trial (RCT) will determine whether the algorithmic auditory stimulation delivered by the CR® neuromodulation device has significant benefit over a placebo stimulus delivered by the same device.

### Primary objectives

• Does CR® neuromodulation significantly reduce tinnitus intrusiveness compared to an active placebo control?

### Secondary objectives

• Does CR® neuromodulation significantly change the percept of tinnitus compared to an active placebo control?

• Does CR® neuromodulation significantly alter neural temporal firing patterns, as measured by spontaneous low-frequency oscillatory responses in the brain (electroencephalography (EEG)), compared to the placebo control?

## Methods/Design

This is a two-center, double-blind, placebo-controlled study with minimized allocation of participants to one of two groups. Center 1 is the National Institute for Health Research (NIHR) Nottingham Hearing Biomedical Research Unit, Nottingham, UK. Center 2 is the University College London (UCL) Ear Institute, London, UK. Participants meeting the inclusion criteria will be randomized to either the intervention group (Group 1) or the placebo group (Group 2) of a 12-week RCT. After 12 weeks, the placebo group will be unblinded and continue on the study according to the treatment protocol. After the RCT, all participants will be followed for a further 24 weeks in a long-term extension (LTE) arm (Figure 1). The primary endpoints are the pre- and post-intervention metrics that provide the primary measures of efficacy, that is, responses about thoughts and feelings associated with tinnitus measured using a validated questionnaire. Repeated measures of general quality of life, tinnitus handicap (as measured by two other tinnitus questionnaires), resting state EEG, and psychoacoustic measure of tinnitus percept will also be collected as secondary outcome measures.

**Figure 1 F1:**
[figure not shown]
**Trial flow chart.** *Tinnitus assessment will include psychoacoustic (Tinnitus Tester) measures and questionnaire measures in the RCT phase. Tinnitus Tester measures will not be taken in the LTE phase. EEG, electroencephalography; LTE, long-term extension; RCT, randomized controlled trial.

Permission to conduct the study was granted by the National Research Ethics Service (NRES) Committee, East Midlands – Nottingham 1, Nottingham, UK, and the trial sponsor is the Nottingham University Hospitals National Health Service (NHS) Trust, Research and Innovation department, Nottingham, UK.

### Population and sample size

Participants will be recruited through leaflets placed in audiology, and ear, nose and throat (ENT) departments, and any direct contacts made to the recruiting centers in response to publicity in the national media. Written informed consent will be obtained from each participant in accordance with the permissions granted. The primary outcome measure of treatment efficacy is the Tinnitus Handicap Questionnaire (THQ) [17], where the maximum score is 2,700. THQ data from a published study of tinnitus maskers were used to estimate the required sample size (two-sample *t*-test power analysis, performed in *R*). After a 12-week intervention, Henry *et al*. [18] found that a difference in mean THQ score of 194 between groups with a pooled standard deviation (SD) of 450 was considered significant, and represented a medium effect size. If we therefore assume a difference in mean THQ score of 250 between groups with a pooled SD of 425 as representative of a large effect size, then for a two-sided significance level of 0.05 and 80% power, it is estimated that 47 participants are required for each group. We assume a low drop-out rate of approximately 5% in 12 weeks and therefore a total of 100 participants will be recruited.

#### Inclusion criteria

• Men and women ≥18 years of age

• Pure-tone average (PTA) hearing thresholds <60 dB HL (0.5, 1, 2, 4 kHz) in the ear where tinnitus is perceived

• Must be able to hear stimulation tones presented by the device at all frequencies

• Chronic subjective tinnitus for more than 3 months

• Dominant tinnitus frequency measured between 0.2 and 10 kHz

• At least mild tinnitus, score ≥18 on Tinnitus Handicap Inventory (THI) [19]

• Willing to wear the device for 4 to 6 hours daily during the trial

• Sufficient command of English language to read, understand and complete the questionnaires

• Able and willing to give informed consent

#### Exclusion criteria

• Objective tinnitus, Ménière’s disease, temporomandibular joint disorder

• Pulsatile tinnitus

• Intermittent tinnitus

• Severe anxiety, >25 score on the Beck Anxiety Inventory (BAI) [20]

• Severe depression, >29 score on the Beck Depression Inventory (BDI-II) [20]

• Catastrophic tinnitus, score ≥78 on the THI

• Hearing aid wearers for less than 9 months, or long-term hearing aid wearers who have had prescription adjustments within last 3 months

• Pure-tone absolute hearing thresholds >70 dB on individual frequencies up to 8 kHz (unable to sufficiently hear the stimulus)

• Taking part in another trial during the 30 days before study start

• The individually tailored training stimulus is uncomfortable or not acceptable to the participant

Pure-tone audiometry will be conducted in a soundproof booth using the Unity 2 system (Siemens, Berlin, Germany) and HDA 200 headphones (Sennheiser, Wedemark, Germany), measuring hearing thresholds between 125 and 12,000 Hz.

Participants will be withdrawn from the trial at any point if they commence any other form of tinnitus therapy, or if following commencement of the study they report an adverse event. The definition of an adverse event in the context of this study is either: 1) since wearing the device tinnitus intrusiveness increases and makes it unbearable; or 2) a disease or symptom (unrelated to tinnitus) present at baseline worsens following the start of the study.

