**Figure 3 F3:**
[figure not shown]
**Device fitting protocol for differences in tinnitus percept between ears.** If tinnitus is identified as central (not in the ear) then only one ear need be assessed.

Participants will be reassessed at planned intervals over the 36 weeks of the trial (Figure 1), or at an interim interval if they experience a noticeable change in tinnitus pitch. The device prescription will be reassessed at each visit, and when there is a change in tinnitus pitch it will be adjusted accordingly. When a participant’s tinnitus pitch is increased beyond the output limits of the device, that is, tinnitus at or above 10.5 kHz, the participant will pause using the device for 2 weeks, and will then be reassessed. If at this assessment tinnitus remains at or above 10.5 kHz, the participant will be withdrawn from the trial.

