### Statistical methods, data analysis and reporting

Analysis will be performed to include all 100 participants who meet the study criteria and are fitted with the device. Participants leaving the study before its completion will not be replaced. Any missing data will be imputed using an expectation-maximization method, which assumes a normal distribution for the partially missing data and bases inferences on the likelihood under that distribution (maximum 25 iterations, performed in SPSS v16.0, IBM, Armonk, USA). Effect sizes will be calculated with Cohen’s *d* computed with the pooled SD of the two groups.

Following completion of the trial, the sponsor will use all reasonable endeavors to ensure the appropriate publication of the research. The manufacturer’s approval of the manuscript will be sought prior to submission. However, the investigators have the right to publish results of the statistical analysis, conducted according to the protocol, whether they are positive or negative, and whether they support or negate the commercial interests of the manufacturer.

Baseline characteristics of participants will be reported as descriptive statistics, including but not limited to age, gender, hearing levels, anxiety, depression, medication, tinnitus duration, tinnitus severity, tinnitus dominant pitch, and tinnitus loudness estimates. Comparisons between groups will assess the degree to which comparability of randomization was achieved.

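### Withdrawal from the trial for unbearable tinnitus or for starting another therapy, followed by EM imputation, can bias the week-12 THQ comparison in either direction if withdrawals differ by arm

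*Protocol article*

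**What the plan says.** All references are to the protocol article.

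- **Primary objectives** asks: "Does CR® neuromodulation significantly reduce tinnitus intrusiveness compared to an active placebo control". **Primary outcome measure** makes this the change in THQ from baseline to week 12.
- **Exclusion criteria**, closing paragraph, gives the withdrawal rule: "Participants will be withdrawn from the trial at any point if they commence any other form of tinnitus therapy", continuing "or if following commencement of the study they report an adverse event". There are two definitions of an adverse event: "since wearing the device tinnitus intrusiveness increases and makes it unbearable", and "a disease or symptom (unrelated to tinnitus) present at baseline worsens following the start of the study".
- **Device fitting procedure** adds a rule for pitch beyond the device's output, after a two-week pause: "If at this assessment tinnitus remains at or above 10.5 kHz, the participant will be withdrawn from the trial".
- **Statistical methods, data analysis and reporting** analyses all 100 eligible participants fitted with the device and does not replace leavers. It then states: "Any missing data will be imputed using an expectation-maximization method", under a normal likelihood.
- **Population and sample size** allows for about 5% drop-out over the 12 weeks.
- **Safety analysis** has adverse events recorded and reported under the sponsor's procedure.

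**The concern.** The rules end participation in the trial, not only use of the device. Two of the triggers bear on the primary outcome. Unbearable intrusiveness is itself a very poor result on the primary construct. Starting another tinnitus therapy is plausibly a response to a poor result. The scores most likely to be missing at week 12 are therefore among the worst.

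EM under a normal model is valid when missingness depends only on what has been observed. Here the protocol lets it depend on a deterioration that may not have been captured on the THQ before the participant leaves. The imputed score then tends to be better than the true one, and the arm with more such withdrawals looks better than it should.

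Either direction is possible. Worsening specific to the active sound would remove more from the treatment arm. A placebo predicted to lack the therapeutic effect (Placebo control) may lead more placebo participants to seek other therapy.

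**Working it through.** **Step 1. The plan's own figure.** Population and sample size gives a difference of 250, SD 425, two-sided 5% and 80% power. The effect size is d = 250/425 = 0.588. The two-sample t-test needs 46.35, rounded up to 47 per group. Allowing 5% loss, 47/0.95 = 49.5, so 50 per group and 100 in total. The stated figures reproduce.

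**Step 2. Algebra of the bias.** Let w_T and w_P be the shares withdrawn for outcome-related reasons, and g the number of THQ points by which a leaver's true change is worse than the imputed one. Each arm mean is too favourable by w × g, so

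overstatement of benefit = (w_T − w_P) × g.

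The document gives neither w nor g, so both are assumed.

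| Excess withdrawn in one arm | g = 300 | g = 600 |
|---|---|---|
| 1 of 50 (2%), e.g. 3 against 2 | 6 | 12 |
| 3 of 50 (6%), e.g. 4 against 1 | 18 | 36 |
| 5 of 50 (10%), e.g. 5 against 0 | 30 | 60 |

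Against the 250-point target, 18/250 = 7% and 60/250 = 24%. In SD units, 18/425 = 0.04 and 60/425 = 0.14. The three examples all have 5 leavers in 100, which is the planned loss. What changes is how they divide between the arms. At 3 against 2 the bias is 6 to 12 points (2 to 5% of the target).

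**Step 3. Simulation.** Assumptions: 50 per arm, change SD 425, baseline-change correlation of size 0.5, 4,000 runs, and the worst changes in each arm set missing. Missing values were replaced by a regression of change on baseline fitted to the observed participants of both arms. This is a simplified stand-in for EM: it uses the leaver's baseline but no interim scores.

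| Withdrawn T / P | True effect | Estimate, all data | Estimate, imputed | Rejection, all data | Rejection, imputed |
|---|---|---|---|---|---|
| 6% / 6% | 0 | −2 | −2 | 4.5% | 7.2% |
| 10% / 2% | 0 | 0 | +45 | 5.0% | 10.7% |
| 2% / 10% | 0 | +1 | −44 | 4.9% | 11.1% |
| 10% / 0% | 0 | −2 | +58 | 5.2% | 12.7% |
| 10% / 2% | 250 | 251 | 280 | 82.7% | 94.3% |
| 2% / 10% | 250 | 251 | 190 | 83.3% | 68.9% |
| 6% / 6% | 250 | 249 | 235 | 83.3% | 85.9% |

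The 10%/0% row implies g of about (57.5 + 1.5)/0.10 = 590, near the top of the range in Step 2. Making every leaver the worst of their arm is thus a severe case. The drop to 235 in the last row matches 0.06 × 250 = 15, because the imputation had no term for arm. The article does not say whether the EM model would have one. With week-12 scores observed for everyone, the estimates are unbiased and rejection under no effect is 4.5 to 5.2% in the rows shown.

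**The case against.** Much of the opposing case stands and limits the point.

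- A reader might infer that the rule hides harm. It does not: unbearable intrusiveness is by definition an adverse event, and Safety analysis has such events recorded and reported. Only the THQ comparison can be distorted.
- A reader might infer that anyone who gets worse is removed. The trigger is worsening that becomes unbearable; lesser worsening stays in the data.
- A reader might treat every withdrawal trigger as driven by the outcome. The 10.5 kHz rule reflects a device limit, and nothing in the article ties pitch to the THQ. The second adverse-event definition is expressly unrelated to tinnitus. Both add to the loss of data but are not shown to depend on the primary construct.
- A reader might suppose that leavers are imputed purely from those who stayed. EM can also use the leaver's own baseline and any earlier scores. If worsening was recorded before withdrawal, part of the bias goes. The visit schedule is in a figure not available here.
- That no week-12 THQ is obtained after withdrawal is an inference from the wording. The full protocol may provide for it, and for sensitivity analyses.
- A reader might conclude that no analysis could help afterwards. A missing-not-at-random sensitivity analysis could bound the bias, though it cannot replace the missing scores.
- The imbalances are assumed. An excess of 3 to 5 needs most or all of the planned 5% loss to fall in one arm.

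What remains is that the article states a rule ending trial participation on an extreme primary-construct result, together with an imputation method that assumes such missingness is ignorable.

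**Conclusion.** The point holds as a weakness in how the withdrawal rule and the missing-data method fit together. Followed as written, and if week-12 THQ is not collected after withdrawal, the primary difference is biased towards the arm with more outcome-related withdrawals. With an assumed excess of 3 to 5 of 50 and a gap of 300 to 600 points, the bias is 18 to 60 THQ points (7 to 24% of the target). The harsher simulated case of 10% against 2% raised the false-positive rate to about 11%, and the reverse imbalance cut power to 69%. The bias is modest if the planned 5% loss is spread over both arms, and near zero if withdrawals are balanced and there is no effect. The documents do not show that it will occur. The case for acting is that the remedy is cheap and secures data that analysis can only approximate later.

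**What to change.** Leave the device-stopping criteria unchanged. In Exclusion criteria and in Device fitting procedure, separate stopping the device from leaving follow-up:

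1. State that a participant who meets a criterion stops the device but remains in follow-up unless consent is withdrawn. If the full protocol already provides for this, say so.
2. Collect the THQ, with THI and TFI, at week 12 from every randomised participant who has not withdrawn consent, by post if needed. Use the observed values in the primary analysis.
3. Record the reason and date of stopping, and report them by arm, including the number starting another tinnitus therapy.
4. Add a missing-not-at-random sensitivity analysis for scores still missing, for example by making imputed changes worse by a stated range of THQ points in each arm.

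The cost is a short amendment and a few extra questionnaires; Trial status says recruitment is under way. There is also a price in interpretation: the estimate will include time off the device and any effect of other therapy, which can dilute or mask the device effect. The counts by arm in item 3 let the reader judge this.

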### Secondary outcome measures

#### Questionnaires

The World Health Organization (WHO) Quality Of Life-BREF (WHOQOL-BREF) is a 26-item questionnaire measuring self-perceived quality of life in four domains (physical health, psychological, social relationships, environment) with test-retest reliability of 0.66 to 0.80 [25].

In the UK, the THI is the most common clinical tool used for diagnosis, and sometimes outcome assessment [26]. It is a 25-item measure of tinnitus severity with test-retest reliability of 0.93.

We will also add the Tinnitus Functional Index (TFI) questionnaire [27] to the assessment battery. This 25-item questionnaire was very recently developed as a sensitive measure of treatment-related change in tinnitus distress with a clinically significant change defined at 13 points. It is also a diagnostic tool for tinnitus severity with high test-retest reliability of 0.97.

Participants will also be provided with a paper diary and asked to log their daily use of the device, and note any experience or comment on its usability.

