### Safety analysis

Adverse events that occur during the trial will be recorded and reported according to the trial sponsor’s standard operating procedure (SOP) for medical device trials (Nottingham University Hospitals NHS Trust SOP 52).

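### Tinnitus worsening enters the safety count only when the participant finds it unbearable; a TFI rise of 13 points or more does not, and no count of worsened participants by arm is stated

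*Protocol article*

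**What the plan says.** The adverse event definition closes the Exclusion criteria section of the protocol article and has two limbs. The first is met when "since wearing the device tinnitus intrusiveness increases and makes it unbearable". The second is met when "a disease or symptom (unrelated to tinnitus) present at baseline worsens following the start of the study". The same definition triggers withdrawal: a participant leaves the trial "if following commencement of the study they report an adverse event".

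The Safety analysis section is one sentence: "Adverse events that occur during the trial will be recorded and reported", under a sponsor procedure (SOP 52) that is not shown.

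The Questionnaires section describes the TFI as a "sensitive measure of treatment-related change in tinnitus distress with a clinically significant change defined at 13 points". It does not say whether that figure refers to improvement, worsening or both. The Methods/Design section and the note to Figure 1 indicate that the tinnitus questionnaires are repeated during the 12-week randomised phase.

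The Efficacy analyses section plans within-group and between-group comparisons of the primary and secondary outcomes, which include THQ, THI and TFI. Its only mention of clinical significance concerns the subgroup that improves most.

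**The concern.** The definition joins two conditions: intrusiveness must increase, and the result must be unbearable. Unbearable is tied to no score. Worsening that stops short of it fails the first limb, and the second limb cannot catch it because it is confined to conditions other than tinnitus. The article nevertheless contains a measured threshold for clinically significant change in tinnitus distress, on a scale it already plans to collect, and applies it to harm nowhere.

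At stake is what the trial can say about harm. It could truthfully report few tinnitus-related adverse events while a noticeable share of participants had TFI rises of 13 points or more. Comparing mean scores would not reveal this if a worsening minority is offset by participants who improve.

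A second effect compounds the first. Participants who do call their tinnitus unbearable are withdrawn, and the Statistical methods section imputes missing data by expectation-maximization under a normal distribution. The week-12 scores of the most severely worsened participants may therefore be model values and not observations.

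**Working it through.** **1. Which worsening reaches the safety count**

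| Participant at week 12 | Limb 1 (increase and unbearable) | Limb 2 (not tinnitus) | Adverse event? |
|---|---|---|---|
| TFI up by 13 or more, not felt to be unbearable | not met | does not apply | no |
| TFI up by less than 13, felt to be unbearable | met | does not apply | yes |
| TFI up by 13 or more, felt to be unbearable | met | does not apply | yes |

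The first row is the gap. It follows from the definition as written and needs no assumption.

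**2. Arm size**

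The article disputes no figure here; the check only fixes the number per arm. Inputs from Population and sample size: difference 250, SD 425, two-sided 5% level, 80% power.

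- Standardised difference: 250 / 425 = 0.588.
- The two-sample t-test calculation gives 46.35, rounded up to 47 per group, as the article states.
- Allowing 5% drop-out: 47 / 0.95 = 49.5, so 50 per arm and 100 in total, again as stated.

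**3. How many participants the gap could involve**

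The documents give no distribution for TFI change, so this is an illustration over an assumed range. Take change as normal with mean m (negative means improvement) and standard deviation SD. The share rising by at least 13 points is 1 − Φ((13 − m)/SD).

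| Assumed SD | m = 0 | m = −5 | m = −10 |
|---|---|---|---|
| 13 | 15.9% (7.9 of 50) | 8.3% (4.2) | 3.8% (1.9) |
| 15 | 19.3% (9.7) | 11.5% (5.8) | 6.3% (3.1) |
| 20 | 25.8% (12.9) | 18.4% (9.2) | 12.5% (6.3) |
| 25 | 30.2% (15.1) | 23.6% (11.8) | 17.9% (8.9) |

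Example, lowest cell: (13 + 10)/13 = 1.77, upper tail 3.8%. Even with a mean improvement of 10 points, about 4% to 18% of an arm would rise by 13 or more. Some of these participants would also call their tinnitus unbearable and be counted, so the table bounds the number exposed to the gap and does not estimate the number missed.

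**4. What a table by arm could show with 50 per arm**

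Power for two proportions, with the pooled variance under the null:

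- 5% versus 15% (assumed). Null SE = √(2 × 0.10 × 0.90 / 50) = 0.0600. Alternative SE = √((0.05 × 0.95 + 0.15 × 0.85)/50) = 0.0592. Power = Φ((0.10 − 1.96 × 0.0600)/0.0592) = 38%.
- 10% versus 30% (assumed). Null SE = √(2 × 0.20 × 0.80 / 50) = 0.0800. Alternative SE = √((0.10 × 0.90 + 0.30 × 0.70)/50) = 0.0775. Power = 71%.

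An observed 15% versus 5% would carry a 95% interval for the difference of about 10 ± 1.96 × 5.92 = 10 ± 11.6 percentage points. The table would be mainly descriptive.

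**The case against.** The strongest reply is that tinnitus worsening is not ignored. TFI, THI and THQ are compared between randomised arms at week 12, and the listed methods include McNemar's test and generalized linear models, so categorical analyses are contemplated. This stands in part. A reader might infer that worsening is never compared between arms, and the Efficacy analyses section rules that out. What the article does not state is a count of participants who worsened.

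A second reply is that a deterioration table is ordinary SAP content, and that neither the SAP nor SOP 52 is shown. If a missing table were the whole point, that would settle it. The point rests on a rule the article does state: its definition decides what is an adverse event in this study. If SOP 52 uses a broader definition, the two conflict and need reconciling.

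Three further inferences are tempting and not supported:

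- **A THI worsening cut-off.** "Catastrophic tinnitus, score ≥78 on the THI" is an exclusion limit and "At least mild tinnitus, score ≥18 on Tinnitus Handicap Inventory (THI" an entry limit. The article gives no THI threshold for change. Only the TFI figure is one.
- **Arms that cannot be compared.** A personal threshold such as unbearable varies between people. Participants, outcome assessors and fitting audiologists are blinded, so this lowers sensitivity and adds noise but does not by itself bias the comparison.
- **Worsened tinnitus as the device's main risk.** The article ranks no device risks.

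It is also fair to say that some rises of 13 points would be ordinary fluctuation. That is a reason to show both arms side by side.

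**Conclusion.** The concern holds in a limited form. As written, the definition admits tinnitus worsening to the safety count only when it is unbearable. A TFI rise that meets "a clinically significant change defined at 13 points" is not enough, and the article states no count by arm of participants who worsen. The outcome comparison would show a shift in average scores, but need not show a worsening minority.

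The gap itself follows from the text alone. Its size does not: the range of about 4% to 30% of an arm (2 to 15 of 50) depends on an assumed normal TFI change with SD 13 to 25 and mean between zero and a 10-point improvement. Applying the 13-point figure to worsening is also a choice, since the article gives no direction for it.

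This is a cheap improvement to what the trial can conclude about harm. It does not invalidate the primary analysis or the sample size.

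**What to change.** Add to the week-12 safety analysis a descriptive table by randomised arm giving the number and proportion of participants whose TFI rose by 13 points or more from baseline, with a 95% confidence interval for the difference.

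- Base it on observed scores, and state how many week-12 TFI scores are missing in each arm.
- Show participants withdrawn for unbearable tinnitus as worsened, on a line of their own and in the total, without relying on imputed scores.
- THI of 78 or more at week 12 may be added as a supplement, labelled as the trial's entry limit and not as a validated worsening threshold.

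Reconcile the adverse event definition under Exclusion criteria, the TFI threshold under Questionnaires and the Safety analysis section, so that the reader knows which worsening is reported as harm. The table is a reporting outcome and is separate from the adverse event and withdrawal rule, to which no change is proposed.

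The cost is a sentence in the plan and one table from scores already collected. The reported number of participants with worsened tinnitus may be higher, and with about 50 per arm the comparison has low power and should be presented as descriptive.
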